#### Secondary outcomes

Secondary outcomes will be Bath Ankylosing Spondylitis Disease Activity Index (BASDAI), Bath Ankylosing Spondylitis Function Index (BASFI), Fatigue Scale-14 (FS-14) results. The BASDAI and BASFI were developed in 1994 using the Visual Analog Scale (VAS) [43, 44]. The BASDAI is a patient-generated index measuring disease activity in patients with AS. The index includes 6 items reflect levels of back pain, fatigue, peripheral joint pain and swelling, localized tenderness, and the duration and severity of morning stiffness. Visual analog scale (VAS, 0–10 cm) anchored by adjectival descriptors “none” and “very severe,” stiffness is anchored by a time scale (0–2 or more hours). The scores for questions 5 and 6 (severity and duration of morning stiffness) are averaged, and the result is then averaged with the remaining 4 question scores to give a final score out of 10. The total scores range from 0 (no disease activity) to 10 (maximal disease activity), and a cut off of 4 is used to define active disease. Internal consistency is good with a Cronbach’s α of 0.84–0.87 [45]. For validity, the BASDAI correlated well with the earlier Bath Disease Activity Index with no significant differences in score distribution, reproducibility, or sensitivity. The BASFI is a patient self-report questionnaire, includes 10 items to measures patients’ functional ability in terms of bending, reaching, changing position, standing, turning, and climbing steps. The overall index score is the sum of the individual scores, with higher scores reflecting greater functional impairment. Internal consistency is excellent, with Cronbach’s α reported at 0.936 [46]. And have good evidence of validity through comparison with instruments that measure similar or related constructs, and with measures of mobility. The FS-14 measures severity of physical and mental fatigue during their usual daily activities over the past week, which correlates positively with fatigue severity in AS. The FS-14 is a short questionnaire that asks endorsement (yes/no) of 14-item, easy to administer tool, and with good reliability and validity.

#### Other outcomes

Participant characteristics of age, weight, body mass index, current medical issues, current medications, and back pain history will be collected using electronic case report forms. Participants will be asked for number and types of medications taken, medication scheduling, and the dose used to self-manage AS symptoms at baseline and at weeks 6 and 12.

### Adverse events

Common treatment-related adverse events include dizziness, local subcutaneous hematoma, continuous post-needling pain, localized infections, and palpitations. Adverse events data will document the occurrence, duration, and severity of adverse reactions (symptoms and signs), and how the event was resolved (or not) during the treatment. Adverse events will be categorized by acupuncturists and related specialists as treatment-related or not within 24h after occurrence. If a participant reports a severe adverse event, it should be reported to principal investigators and the Institutional Ethics Committee (IEC) of Guangdong Provincial Hospital of Chinese Medicine, and they will decide to unblind and withdraw from the study. According to the situation, they will be referred to the emergency department or receive appropriate treatment. We will collect, assess, and report any spontaneously described adverse events from participants.

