### Follow-up

Follow-up will occur 12 weeks after completion of the treatment program. This time point was selected to assess sustained long-term effectiveness of the intervention.

The trial work plan is summarized in Fig. 2.

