### Data management and monitoring

The case report form (CRF) includes observation time points, outcome measures, adverse events, and safety evaluations. The outcome assessors will be required to follow the requirements of the CRF and fill in the relevant information in a timely and accurate manner. The data collection and entry will be performed independently by two of the staff members and finalized by a third staff member. The main investigators, acupuncturist, sonographers, and laboratory staff will not be involved in data collection. Data will be obtained from the case record form (CRF), and only members of the trial team have access to the CRFs and perform double-data entry. The paper data will be saved with identification codes in seal. The electronic data will be stored in the ResMan Research Manager. Anonymized trial data will be shared with other researchers at least 3 years after the article is published. If reviewers or readers have any questions regarding our published data, they can contact the corresponding author for access to original data or visit ResMan (http://www.medresman.org/uc/project/projectadd.aspx). We will be monitored by the IEC of Guangdong Provincial Hospital of Chinese Medicine, and it is independent from the investigators and sponsor which will audit trial conduct every 12 months. And any modifications and corrections to operation procedures will be fully documented using a breach report form, monitored, and submitted to the directors of the ethics committee and China Clinical Trial Registration.

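### Spontaneous report is the only way of eliciting adverse events that the article names; the five expected events are tied to no question, and collection at the week-24 follow-up is not stated

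*Protocol article*

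**What the plan says.** The Adverse events section of the protocol article gives the expected events: "Common treatment-related adverse events include dizziness, local subcutaneous hematoma, continuous post-needling pain, localized infections, and palpitations". It says that occurrence, duration and severity will be documented, together with "how the event was resolved (or not) during the treatment". On causality it says: "Adverse events will be categorized by acupuncturists and related specialists as treatment-related or not within 24h after occurrence". The escalation rule for severe events starts from a participant reporting one. The section closes with the only sentence on how events come to light: "We will collect, assess, and report any spontaneously described adverse events from participants".

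The Data management and monitoring section adds: "The case report form (CRF) includes observation time points, outcome measures, adverse events, and safety evaluations". Outcome assessors complete the form and must "fill in the relevant information in a timely and accurate manner". The same section keeps acupuncturists out of data collection, and the Abstract says the outcome assessor is blinded to allocation.

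The Follow-up section says: "Follow-up will occur 12 weeks after completion of the treatment program". The caption of Fig. 2 places this at 24 weeks. The reason given is: "This time point was selected to assess sustained long-term effectiveness of the intervention". Safety is not mentioned there.

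**The concern.** The article names a passive method for harms and no active one. Patients often do not volunteer minor, expected effects such as a bruise, soreness that persists after needling, or brief dizziness, particularly if they regard them as a normal part of treatment. Four of the listed events are of a kind that can be mild and pass quickly, so the list and the method fit each other poorly.

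What is at stake is how a low count is read. The Background already describes acupuncture as safe with few side effects. A short list of volunteered events from two arms of 30 could easily be taken as confirming this, when it may partly reflect that nobody asked. The week-24 contact raises a smaller question: it is justified by effectiveness alone, and a reader cannot tell whether harms are recorded there.

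**Working it through.** The check is mainly textual. The article states no adverse event rate, so there is no figure of its own to reproduce.

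**1. Elicitation.** Three parts of the article bear on how events become known.
- The Adverse events section refers to spontaneous description, and its severe-event rule also depends on a participant report.
- Data management and monitoring says where events are recorded (the case report form) and who completes it (the outcome assessors). It does not say that patients are questioned.
- Elsewhere the authors say so when they intend to ask. Under Other outcomes, participants are to be asked about medication at baseline and at weeks 6 and 12. Under Blinding, they answer a questionnaire after the last treatment. No comparable statement exists for adverse events.

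So spontaneous report is the only elicitation method named. Others are not excluded.

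**2. Window.** The one time phrase in the Adverse events section is in "how the event was resolved (or not) during the treatment". It most naturally describes how the outcome of an event is documented. It is not a stated start or end of collection. Follow-up and the Fig. 2 caption fix a contact at week 24 without saying whether events are recorded there. Collection at week 24 is therefore unstated.

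**3. What a low count can show (illustration on assumed values).** Let p be a patient's true risk of a given event and c the overall fraction of affected patients whose event reaches the form. With n = 30 per arm (Sample size section), the expected count is 30·p·c, and

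P(at least one recorded) = 1 − (1 − p·c)^30.

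The article gives neither p nor c, so a wide range is shown:

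| True risk p | c = 1 | c = 0.75 | c = 0.50 | c = 0.25 |
|---|---|---|---|---|
| 5% | 0.785 | 0.682 | 0.532 | 0.314 |
| 10% | 0.958 | 0.904 | 0.785 | 0.532 |
| 20% | 0.999 | 0.992 | 0.958 | 0.785 |

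Two things follow that do not depend on choosing a particular c.
- Even at full capture, a 5% risk leaves 1 − 0.785 = 0.215 as the chance that an arm records no event.
- The data inform only the product p·c. A 10% risk at half capture and a 5% risk at full capture both give 30 × 0.05 = 1.5 expected events and the same 0.785. The trial's own counts cannot show which of the two applies, so under-capture would not be visible in the results.

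The table shows what under-capture would do. It does not show that it happens in this trial.

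**The case against.** The strongest reply is that this reads too much into one sentence of a condensed article. The sentence includes volunteered reports and excludes nothing. The section speaks of signs as well as symptoms, and a hematoma or local infection can be observed without being volunteered. The case report form carries safety evaluations, completed by assessors. With 2–3 sessions a week for 12 weeks there are 24 to 36 contacts (2 × 12 to 3 × 12) at which an event could surface. The schedule and work-plan figures are not shown, and safety is not among the stated hypotheses.

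Much of this stands, and it rules out several stronger readings:
- A reader might infer that events come from spontaneous reports alone. The article does not say so; it merely names no other method.
- A reader might infer that the follow-up is missed. That would rest on silence, on a phrase about resolution, and on figures that are not available here.
- A reader might infer that harms will be under-counted by a known amount, or differently by arm because the acupuncturist hears the reports. The documents give no capture fraction and do not say who receives a volunteered report. Acupuncturists are kept out of data collection, although they do help to classify causality.

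It does not remove the point. A place on the form and frequent contact are not a question put to the patient. The choice of spontaneous description is stated, so this is more than detail left to a fuller document. Needling events mostly arise close to treatment, so the week-24 contact will add less than the visits during treatment.

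**Conclusion.** The point holds in a limited form. The article names unprompted report as its method for harms, ties its own list of five events to no question, and leaves collection at week 24 unstated. A better method is available at visits already planned. If the text stays as it is, a low adverse event count in 30 patients per arm should be treated as weak evidence of safety.

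No size can be put on any under-count; the illustrated probabilities rest entirely on assumed risks and capture fractions. The conclusion also assumes that the full protocol contains no active questioning that the article leaves out. If it does, the remedy shrinks to saying so in the Adverse events section. The primary outcomes, the sample size and the efficacy inference are not affected. This is a change that should be made, but the trial's main conclusion does not depend on it.

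**What to change.** In the Adverse events section, replace reliance on spontaneous description with wording to this effect: at weeks 6, 12 and 24 the blinded outcome assessor asks every participant in both arms the same open question about any new or worsened complaint, then asks about each of the five listed events in turn; events volunteered or observed between visits are also recorded; recording runs from the first treatment to week 24.

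Align the other places with this. Follow-up should say that the week-24 contact also covers adverse events, and Data management and monitoring should say that the case report form carries the question. The 24-hour limit for classifying causality runs from occurrence, so it needs to be reconciled with events first learned of at a scheduled visit. Report prompted and volunteered events separately by arm.

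The cost is a few lines on the form at contacts already planned. More minor events will be recorded, and the paper should say that they were prompted. Recall over six to twelve weeks is imperfect, which is why recording between visits should continue. Separate questioning by another person at every session is not needed; it could require extra staff.

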### Follow-up

Follow-up will occur 12 weeks after completion of the treatment program. This time point was selected to assess sustained long-term effectiveness of the intervention.

The trial work plan is summarized in Fig. 2.

**Fig. 2 Fig2:**
[figure not shown]
Trial work plan. Primary-outcomes measures will be musculoskeletal-ultrasound, ASQoL, Pian-VAS, and BASMI results. The remaining outcome measures will be for secondary outcomes. Follow-up will be performed at 24 weeks

### Sample size

The required sample size for this study was estimated based on a study by You et al. [47]: at the week 24, pain VAS score was 3.87±1.54 (mean ± standard deviation [SD]) in needle-knife group and 4.59±1.57 in the control group. With a conservative estimate of 0.36point difference on a 10-point VAS score between the two arms, and assuming a standard deviation of 0.72 for both arms, based upon a two sample t tests assuming equal variance analysis conducted by an independent statistician via PASS 15.0, a sample size of 23 per group will yield a power of 90% at an alpha (α) value of 0.05. To account for an anticipated dropout rate of 20%, finally, the sample size was inflated to 60 with 30 patients per arm will be sufficient to detect a clinically important difference in this trial.

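### The planning SD of 0.72 for pain VAS equals the difference between the cited means, not the cited SDs of 1.54 and 1.57, so variability is understated more than twofold

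*Protocol article*

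**What the plan says.** The Sample size section of the protocol article rests the calculation on one published study, in which week-24 "pain VAS score was 3.87±1.54 (mean ± standard deviation [SD]) in needle-knife group and 4.59±1.57 in the control group". The article itself labels these figures as mean ± SD.

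It then plans on a "conservative estimate of 0.36point difference on a 10-point VAS score between the two arms", "assuming a standard deviation of 0.72 for both arms". The method is "based upon a two sample t tests assuming equal variance analysis", and the result is that "a sample size of 23 per group will yield a power of 90% at an alpha (α) value of 0.05". After a 20% allowance for dropout the size becomes 30 per arm, 60 in total, which the section calls enough to detect a clinically important difference.

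Pain VAS is one of the primary outcomes and the only one used to size the trial.

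**The concern.** The section names a source, reports its SDs, and in the next sentence uses an SD less than half as large without saying where it came from. The value used coincides to the second decimal with the difference between the source's two means. That points to the effect having been put in the place of the SD.

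The SD enters the sample size squared, so the stated power rests on a variance less than a quarter of the one the source reports. If the cited SD is nearer the truth, the trial has little chance of detecting the difference it says it is designed for, and a null result on pain could be misread as evidence that acupuncture adds nothing over sham.

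This is separate from a second error in the same sentence: 23 per group does not follow from 0.36 and 0.72. Correcting the group size at SD 0.72 would still leave the plan far short.

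**Working it through.** **Inputs (all from the Sample size section).** Means 3.87 and 4.59; SDs 1.54 and 1.57; planning difference 0.36; planning SD 0.72; alpha 0.05; power 90%; 23 per group; dropout 20%; 30 per arm. The section does not say one- or two-sided; two-sided is taken here. Equal group sizes in the cited study are assumed for pooling. Power is from the exact noncentral t distribution for the equal-variance two-sample t test.

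**Step 1: the plan's own figure.** By the normal approximation, n per group = 2(1.960 + 1.282)² × (SD/difference)² = 21.01 × (SD/difference)².

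- Stated inputs: (0.72/0.36)² = 4, so n = 84.06, rounded up to 85 (86 by exact t). Power with 23 per group is 38%. A one-sided test needs 70, and 80% power two-sided needs 64, so none of these variants gives 23.
- Difference 0.72 with SD 0.72 (standardised effect 1.0): exact t gives 23 per group (power 89.97% at 22 and 91.2% at 23). This is the printed number.

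**Step 2: where 0.72 comes from.**

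- 4.59 − 3.87 = 0.72, equal to the planning SD.
- 0.72/2 = 0.36, equal to the planning difference.
- Pooled cited SD = √((1.54² + 1.57²)/2) = 1.555.
- 1.555/0.72 = 2.16, and 2.16² gives a variance ratio of about 4.66.

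**Step 3: the plan with the cited SD.** After 20% dropout, 30 × 0.8 = 24 per arm remain.

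| True difference | Standardised effect | Power, 23/arm | Power, 24/arm | Power, 30/arm | n/arm for 90% |
|---|---|---|---|---|---|
| 0.36 | 0.36/1.555 = 0.23 | 12.0% | 12.3% | 14.3% | 394 |
| 0.72 | 0.72/1.555 = 0.46 | 33.6% | 34.9% | 42.2% | 100 |

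For 0.72 the normal approximation gives 98.03, so 99; exact power at 99 is a hair under 90%, hence 100.

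**Step 4: what the trial can detect with 90% power.** The standardised effect needed is 0.956 with 24 per arm and 0.851 with 30. Multiplied by 1.555 these are 1.49 and 1.32 points, which is 4.1 and 3.7 times 0.36.

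**Step 5: could baseline adjustment give 0.72?** Assume equal SDs at baseline and follow-up.

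- Covariance adjustment: 1.555 × √(1 − r²) = 0.72 requires r = 0.89.
- Change score: 1.555 × √(2(1 − r)) = 0.72 also requires r = 0.89.
- A correlation of 0.7 under covariance adjustment gives 1.555 × √(1 − 0.49) = 1.11.

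**The case against.** Four points can be made for the plan.

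- **The origin of 0.72 is inferred.** The article never says that the difference was entered as the SD, and 0.36 may itself be a misprint, since 0.72 over 0.72 returns exactly 23 per group. This is fair. It makes the power for 0.72 (35% to 42%) the safer headline than the power for 0.36. It does not rescue the plan, because 0.72 is the wrong SD on that reading too.
- **The cited SDs may not carry over.** They come from a needle-knife trial at week 24, while this trial enrols patients in a stable disease period and analyses by repeated-measures ANOVA. So 1.555 is a planning value, not a known one. But it is the only SD the section offers, and the section says it planned from that study.
- **A smaller SD could reflect adjustment for baseline.** The section specifies a plain two-sample t test and mentions neither baseline adjustment nor change scores. The correlation needed, about 0.89, is nowhere claimed.
- **Halving the difference was meant to be conservative.** The understated SD more than cancels it: 0.36/0.72 = 0.50 is larger than the source's own full effect, 0.72/1.555 = 0.46.

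What stands is a caution about certainty over the origin of the figure and about how exactly 1.555 applies here. The contradiction within the paragraph remains.

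**Conclusion.** The concern holds. The planning SD conflicts with the SDs quoted immediately before it and matches the difference in means exactly. The claim of 90% power is wrong as written: power at the planned size is in the range of 12% to 42%, depending on whether 0.36 or 0.72 is the target and on dropout.

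These figures assume a two-sided 5% test, equal arms, a pooled SD of 1.555 and no gain from baseline adjustment, and they apply to pain VAS only. That the difference was entered as the SD is a well-supported inference; the conclusion does not depend on it. The point must be corrected, because the section's statement that the sample is sufficient rests on this SD.

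**What to change.** Rewrite the sample-size paragraph, and correct the group size of 23 in the same revision.

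- Replace 0.72 by the cited pooled SD of about 1.56, and say that it is a planning value taken from a different intervention.
- State that 30 per arm (24 after 20% dropout) gives 90% power for a between-arm difference of about 1.5 points on the 0–10 VAS, about 12% for 0.36 points and about 35% for 0.72 points.
- If a smaller SD is intended because the analysis uses baseline, state the assumed correlation and derive the SD from it.
- Justify a difference of about 1.5 points as clinically important, or withdraw the statement that the sample is sufficient. It is about twice what the cited study observed, and nothing in the article supports it as the target.

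The change is to wording and requires no extra patients, which matters because the Trial status section reports recruitment under way. The price is a much less favourable detectable difference. Keeping 0.36 or 0.72 as the target at 90% power would instead mean about 394 or 100 analysed patients per arm.

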### Data management and monitoring

The case report form (CRF) includes observation time points, outcome measures, adverse events, and safety evaluations. The outcome assessors will be required to follow the requirements of the CRF and fill in the relevant information in a timely and accurate manner. The data collection and entry will be performed independently by two of the staff members and finalized by a third staff member. The main investigators, acupuncturist, sonographers, and laboratory staff will not be involved in data collection. Data will be obtained from the case record form (CRF), and only members of the trial team have access to the CRFs and perform double-data entry. The paper data will be saved with identification codes in seal. The electronic data will be stored in the ResMan Research Manager. Anonymized trial data will be shared with other researchers at least 3 years after the article is published. If reviewers or readers have any questions regarding our published data, they can contact the corresponding author for access to original data or visit ResMan (http://www.medresman.org/uc/project/projectadd.aspx). We will be monitored by the IEC of Guangdong Provincial Hospital of Chinese Medicine, and it is independent from the investigators and sponsor which will audit trial conduct every 12 months. And any modifications and corrections to operation procedures will be fully documented using a breach report form, monitored, and submitted to the directors of the ethics committee and China Clinical Trial Registration.

